## 2.0 **STUDY OBJECTIVES**

The study objectives are:

- To determine the impact of immunisation of a whole community with a pneumococcal polysaccharide/protein conjugate vaccine on nasopharyngeal carriage of pneumococci.
- To determine the effects of vaccination on the prevalence, density, duration and rate of acquisition of nasopharyngeal colonisation with pneumococci of vaccine serotype and of non-vaccine serotype.

- To determine changes in the antigenic and molecular characteristics of pneumococci obtained from the nasopharynx of vaccinated and control subjects.

### **3.0 SELECTION AND ENROLLMENT OF SUBJECTS**

#### **3.1 Inclusion Criteria**

- Resident of one of twenty one Gambian villages

#### **3.2 Exclusion criteria**

- Failure of the family/subject to give consent
- non-residence in the villages,
- declared intent of the family/subject to leave the study area permanently within the following 3 months
- Previous exposure to a conjugate pneumococcal vaccine

A record will be kept of subjects who are excluded and the reason for their exclusion will be noted on a form.

#### **3.3 Enrollment Procedures**

Subjects will be recruited from twenty-one Gambian villages. The purpose of the study will be described at meetings with village elders and other members of the village and what it involves for participants. Before enrolling individual members of the villages the nature of the trial will be fully explained including the treatment, observation details, spectrum of likely side effects, follow-up details and extent of collection of Nasopharyngeal swabs (NPS), saliva and blood sampling.

#### **3.4 Substudies**

Sub studies will take place; these will be all covered in revised consent forms, once approved.

#### **3.5 Co-enrollment Guidelines:**

As is MRC policy, study subjects are encouraged not to be involved in other studies.

### **4.0 CLINICAL AND LABORATORY EVALUATIONS**

#### **4.1 Pre-entry/Entry Evaluations**

##### **4.11 Screening**

Details of the study will be carefully discussed with the subjects, who will be asked to read, or will be read to, and sign (or thumb-print) an informed consent form prior to any study-related evaluations being performed. Translations into the local languages will be provided. The subjects that agree to enroll and have signed consent documentation will be enrolled for the study.

##### **4.12 Entry**

Subjects will be excluded based on the criteria enumerated above (Section 3.2).

## 4.2 Evaluations During study

### 4.2.1 Screening at the villages

- Inclusion/exclusion criteria will be checked.
- Written informed consent will be obtained.
- Subject Exclusion Form will be filled by the field supervisor for all subjects excluded from the study
- A nurse field worker will fill the Subject Status Form for all subjects recruited
- Nurse field workers will administer conjugate pneumococcal vaccine to all children up to the age of 30 months.
- In group 1 villages, subjects older than 30 months will receive one dose of conjugate pneumococcal and their equivalent in group 2 villages will receive one dose of the meningococcal polysaccharide C conjugate vaccine.
- Vaccine ID will be included on subjects identity card
- All subjects will be asked to report all health related complaints to the field team.
- 5ml blood and saliva specimen will be obtained from 200 selected subjects following the corresponding SOP.
- Specimens will be put in cool boxes and transferred to the MRC microbiology laboratory on the same day as collection.
- For any specimen, if an individual refuses, we will select the next person on the list supplied by the data room. For those who are travelled we will try and capture them for sampling but after 2 weeks if unsuccessful, will sample the next person on the list.

### 4.2.1 Scheduled follow-up

Infants aged between 2 and 11 months will receive two additional doses of the pneumococcal conjugate vaccine (PCV) at monthly intervals.

Children aged between 12 and 30 months will receive a second dose of PCV a month after the initial dose.

At three, twelve and twenty-four months after the scheduled round of vaccination, nasopharyngeal swabs will be collected from approximately 1,250 subjects, ensuring coverage of each age group and all villages in the cross-sectional survey. These subjects will be selected randomly as described in section 1.4 and separate randomisation procedures will be undertaken for each survey; subjects included in a previous survey will not be excluded. 5ml blood and saliva specimens will be obtained from 200 selected subjects as described in section 1.4.

NPS will be collected weekly from all new births into all the villages until the age of 2 months when they receive the first doses of the pneumococcal conjugate vaccine

NPS will be collected monthly from 430 selected subjects as described in section 1.4.

All new births into the twenty-one villages will receive three doses of pneumococcal conjugate vaccine at monthly intervals from the age of two months.

In the lifetime of the study, new settlers in the villages will be identified and recruited for the study. The same vaccination schedule will apply.

All laboratory procedures will be described in SOPs.

## 4.3 Subjects who prematurely discontinue the study

Subjects, who leave the study at any time, may do so without repercussions. They may still access medical care provided by the study team, and will not be turned away.

## **5.0 DATA COLLECTION AND MONITORING AND ADVERSE EXPERIENCE REPORTING**

### **5.1 Records to Be Kept**

A regulatory folder and a protocol deviations folder will be established.

All filled in paper forms will be filed in securely by the data manager. Individual medical records will be filed together. All electronically stored data will be stored securely and backed up by the data manager.

### **5.2 Role of Data Management**

The Data manager will be responsible for receiving, entering, cleaning, querying, analysing, and storing the data, which accrues from the study. He will generate queries to be addressed by the investigators and will be responsible for linking the paper and electronic data from the field and the clinic with the paper and electronic laboratory data from the immunology, microbiology, haematology and molecular biology laboratories.

### **5.4 Adverse events reporting**

Everyone vaccinated will be requested to report untoward events to the study team. Adverse events will be recorded as observed by the Investigators or as volunteered by the subject or his/her parent/guardian. Full details will be documented in the CRF whether or not the Investigator or his deputies consider the event to be related to the trial substance.

Serious adverse events (SAEs) that occur during the study or within six months of the vaccinations will be notified immediately by telephone by the principal investigator to the study Safety Monitor. All SAEs identified will then be reported jointly by the research clinician and [name] to the Principal investigator and the study Safety Mmonitor as well as to Wyeth, the vaccine manufacturer, accordingly.

Serious adverse events are defined as an event that:

- results in death;
- is life-threatening (*i.e.*, the subject was at risk of death at the time of the event);
- requires or prolongs in-patient hospitalisation;
- results in persistent or significant disability/incapacity;
- is a congenital anomaly/birth defect.

Minimum details to be given in a telephone report are:

- Name of reporting doctor and contact telephone number.
- Study number.
- Nature of adverse event.
- Subject details (number, initials, sex, date of birth, weight and age).
- Date and time of event.
- Drug history.
- Other relevant history.
- Outcome.
- Causality.

The event will be documented on the SAE page of the CRF and reported as appropriate. After the ethics committee's response to the SAE is received, the Principal Investigator and Clinical Monitor will meet to determine the future plan for the study, which could involve amending the protocol, discontinuing the administration of the vaccine, or continuing unchanged for the other volunteers.

## 6.0 STATISTICAL CONSIDERATIONS

### 6.1 General Design Issues

Villages will be randomly assigned to a study group. A computer-generated list of random numbers will be used to assign villages to PCV group (Group 1) or Mening C group (Group 2). Nurse field workers will administer the vaccines.

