## 1.4 Study Design

This study is a single-blind placebo-controlled community randomized trial. All residents of selected 21 Gambian villages are eligible including those born during the study.

All children of the trial community between 2 months of age up to the age of 30 months will receive the seven-valent pneumococcal conjugate vaccine (PCV):

- Subjects born during the study will receive three doses of the vaccine to be given monthly at the ages of 2, 3 and 4 months.
- Subjects between the age of 2 and 11 months will receive three doses of the vaccine to be given monthly
- Children aged between 12 and 30 months will receive two doses at monthly intervals.

The 21 villages will be randomly assigned to one group of 10 villages and one group of 11 villages according to the randomisation SOP. All subjects above the age of 30 months will receive either one dose of PCV or one dose of a meningococcal polysaccharide C conjugate vaccine. The vaccination campaign will be village by village according to an SOP. Because of vaccine pre-labelling differences, nurse field workers administering vaccine will be able to tell which vaccine they are giving. The field team will not communicate the vaccine allocation to other parties. Biological samples will have unique identifiers and will show no information regarding the vaccine received or the participants. Safety of vaccination will be monitored by nurse fieldworkers and study clinician according to an SOP.

3, 12 and 24 months after the first vaccination, cross-sectional surveys will be conducted. The sample for each survey will be obtained through a random sampling method that ensures coverage of all age groups and all villages. This will be described in detail in an SOP. Each subject will have an NPS taken. 5ml blood and saliva specimens will be obtained from 200 subjects, selected according to a corresponding SOP before vaccination and then at the 3, 12 and 24 month time-points. The selected subjects will be distributed across the study villages stratified by age to ensure that 50 come from children in the age range 30 months to 5 years, 50 from children 6 to 15 years, 100 from those aged >15 years.

NPS will be collected from all children born in the population during the study period. An NPS will be collected as soon as possible after birth and then at weekly intervals until the first dose of vaccine at 2 months.

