### 6.3 Sample Size and Accrual

The baseline survey showed that the prevalence of nasopharyngeal carriage with pneumococci of the seven valent vaccine serotype was about 40% in infants up to the age of 2.5 months (the age when the first dose of pneumococcal conjugate vaccine will be given) and 30% in those aged 30 months or more. The coefficient of variation between villages was 0.3. Based on these assumptions and assuming that 50 subjects are studied in each village the trial will have over 90% power with a type 1 error of 5% to detect a 50% reduction in the overall prevalence of pneumococci of vaccine serotype in those over the age of 30 months (prevalence 30% to 15%) and a similar power to detect a 50% reduction in the colonisation of infants with pneumococci of vaccine type before the age of 2 months (prevalence reduced from 40% to 20%). The prevalence of type 1 and type 5 carriage was very low in the initial survey so the study is not specifically powered to detect an increase in carriage with pneumococci of these serotypes but it would detect this if the effect was marked.

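### No balance constraint on village baseline carriage, and no baseline-adjusted analysis, is described for the allocation of 21 villages

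*Combined protocol and SAP*

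**What the plan says.** All references are to the combined protocol and SAP.

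- **Allocation.** Section 6.1: "A computer-generated list of random numbers will be used to assign villages to PCV group (Group 1) or Mening C group (Group 2". Section 1.4: "The 21 villages will be randomly assigned to one group of 10 villages and one group of 11 villages according to the randomisation SOP". The SOP is not among the documents. Neither section mentions stratification, matching or a balance limit.
- **Baseline data.** Section 1.2 reports that a carriage study has already begun in 21 villages. Section 6.3 gives vaccine-type prevalence that "was about 40% in infants up to the age of 2.5 months" and "30% in those aged 30 months or more", and adds: "The coefficient of variation between villages was 0.3". No village-level values are listed, and nothing says that they will be used in allocation or analysis.
- **Power.** Section 6.3, "assuming that 50 subjects are studied in each village", claims more than 90% power at a 5% error level to detect a halving of prevalence: 30% to 15% in those over 30 months, and 40% to 20% in young infants.
- **Analysis.** Section 6.4 describes the main analyses in one general sentence. It names no cluster-level method and no adjustment for baseline.

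**The concern.** With 21 clusters allocated once, chance can leave the arms apart in vaccine-type carriage before anyone is vaccinated. The first outcome listed in section 6.21 is carriage prevalence after vaccination in the same villages, so baseline prevalence is the natural balancing variable. A between-village coefficient of variation cannot be computed without village-level values, so the data evidently exist, although this is inferred and not stated.

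As described, neither the design nor the analysis uses that information. What is at stake is precision, and whether readers will trust one unadjusted comparison of 10 villages with 11 if a baseline gap is visible.

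**Working it through.** **Inputs (sections 1.4 and 6.3).** 10 and 11 villages; between-village CV k = 0.3; m = 50 per village; prevalence p = 0.30 (over 30 months) or 0.40 (young infants); two-sided 5% test (sidedness assumed).

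**1. The plan's own power.** Variance of a village proportion = p(1−p)/m + (kp)².

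- 30% to 15%: control 0.0042 + 0.0081 = 0.0123; PCV 0.00255 + 0.002025 = 0.004575. SE = √(0.0123/11 + 0.004575/10) = 0.0397. Power = Φ(0.15/0.0397 − 1.96) = 96.6%.
- 40% to 20%: control 0.0192; PCV 0.0068. SE = √(0.0192/11 + 0.0068/10) = 0.0492. Power = 98.2%.
- More cautious versions still pass. A noncentral t with 19 degrees of freedom gives about 95% and 97%. Ten villages per arm with one subtracted as a small-sample correction gives 93.4% and 96.1%.

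The stated power holds, with between-village variation included.

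**2. Chance imbalance under simple 10/11 allocation.** SD of the arm difference in true baseline prevalence = kp√(1/10 + 1/11) = kp × 0.437. Tail chances use the normal approximation.

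| | p = 30% | p = 40% |
|---|---|---|
| Village SD (kp) | 9 points | 12 points |
| SD of arm difference | 3.9 points | 5.2 points |
| Median absolute difference | 2.7 points | 3.5 points |
| Chance of more than 5 points | 20% | 34% |
| Chance of more than half the target effect | 6% (over 7.5 points) | 6% (over 10 points) |

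A simulation of 200,000 splits at p = 30%, with beta-distributed village prevalences, gave an SD of 3.9 points, 20.6% above 5 points and 5.7% above 7.5 points.

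**3. Sensitivity to the meaning of the CV.** The figures above take 0.3 as the CV of true village prevalence. If it were instead the CV of observed proportions with 50 swabs per village (an assumption), the true village SD would be √(0.0081 − 0.0042) = 6.2 points. The SD of the arm difference would then be 2.7 points, with about a 7% chance of exceeding 5 points and 0.6% of exceeding 7.5.

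**4. Is restriction feasible?** There are C(21,10) = 352,716 splits. About 39% of them, roughly 136,000, have a true difference of at most 2 points at p = 30%. In practice the limit applies to measured prevalence. With an assumed 50 baseline swabs per village, the chance of a measured difference above 2 points is 68%, so about 32% of splits (roughly 113,000) remain.

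**5. What baseline information could gain.** Let r be the village-level correlation between baseline and follow-up prevalence, which the documents do not give. Multiplying the between-village terms in step 1 by (1 − r²), for 30% to 15%:

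| r (assumed) | SE (points) | Power |
|---|---|---|
| 0 | 3.97 | 96.6% |
| 0.5 | 3.66 | 98.4% |
| 0.7 | 3.34 | 99.4% |

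**The case against.** The best defence is that the risk is already paid for. Chance differences between villages are what the CV of 0.3 represents, power stays above 90% with it included, and simple cluster randomisation is unbiased over allocations. That stands, with one limit: section 6.4 does not commit to a cluster-level test, on which the protection of the type I error depends.

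Several stronger readings are tempting, and the documents do not support them:

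- *The allocation is unrestricted.* Section 1.4 defers the procedure to an SOP that is not supplied. A random-number list is compatible with a constrained or stratified draw. The documents are silent on restriction; they do not state its absence.
- *A sizeable imbalance is likely.* A gap above 5 points is a minority outcome at either prevalence, and a gap above half the target effect has about a 6% chance.
- *Baseline imbalance passes one for one into the estimated effect, and restriction would remove most of it.* Both need a correlation near 1 between baseline and follow-up. At r = 0.5, balance removes only 25% of between-village variance. Under the plan's own halving, the between-village part of the follow-up difference has an SD of √(0.09²/11 + 0.045²/10) = 3.1 points, not 3.9.
- *One arm may be vaccinated earlier in the season.* Section 1.4 places the village-by-village campaign under an SOP, and no seasonal effect on carriage is quantified. This cannot be judged from the documents.

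**Conclusion.** The point holds as a better available method, not as an error that invalidates the trial. For 21 villages the protocol describes no balancing on baseline carriage and no baseline-adjusted analysis, although its own survey evidently supplies the data. Under simple allocation the imbalance in true baseline vaccine-type prevalence is of the size tabulated above: an SD of 3.9 points against a 15-point target effect in those over 30 months, and 5.2 against 20 in young infants.

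These figures assume that 0.3 is the CV of true prevalence and applies at both ages, that the normal approximation holds, and that the SOP adds no restriction. The loss is in precision and credibility. The stated power survives, and a valid cluster-level test keeps its type I error.

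**What to change.** 1. **Section 6.1.** State whether the randomisation SOP restricts allocation. If it does not, use constrained (or stratified) randomisation on village baseline vaccine-type prevalence, and on village size if available. List the 352,716 splits, keep those within preset balance limits, check that the acceptable set is large, and draw one at random.
2. **Section 6.4.** Pre-specify a cluster-level analysis adjusted for village baseline vaccine-type prevalence and any other balancing factor. If allocation has already been done, this step is still available.

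The cost is a short program, some protocol text, and one or two of about 19 degrees of freedom (21 villages less 2 arms). The return depends on the unknown baseline-to-follow-up correlation and could be small if carriage shifts between villages over the 3 to 24 months before the surveys.

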### 6.2 Outcomes of interest

#### 6.21 Impact on carriage

- (a) Differences in the prevalence of nasopharyngeal carriage of pneumococci of vaccine or of non-vaccine serotype in study villages after vaccination in the cross-sectional samples. Differences in the prevalence of carriage with serotype 1 and serotype 5 pneumococci will be of particular importance.
- (b) Acquisition rates of nasopharyngeal carriage in newborns resident in vaccinated or control villages.
- (c) Rate of capsular switching in villages where community wide pneumococcal conjugate vaccination has been introduced, compared to those receiving placebo.

#### 6.22 Pneumococcal IgG and IgA in serum and saliva

This will be determined yes/no antibody assay result, and compared to the carriage results.

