| Phase:                                   | IV                                                                                                                                                                                                                                                                                                                                                                                                                                                                                                                                                            |
| Population:                              | 
Approximately 6000 residents of 21 Gambian villages for vaccination
 
Subsamples of 1250 subjects for evaluation antigenic and molecular characteristics of pneumococci with a subsample of 200 for 5ml blood specimen and saliva.
 
All children born during the study period
 
Subsample of 430 subjects for longitudinal substudy
                                                                                                                                                                                                    |
| Number of Sites:                         | 
Sibanor villages
 
MRC Labs, Fajara, The Gambia
                                                                                                                                                                                                                                                                                                                                                                                                                                                                                                   |
| Study Duration:                          | 36 months (June 2006 until May 2009)                                                                                                                                                                                                                                                                                                                                                                                                                                                                                                                          |

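### Section 6.22 analyses serum and salivary IgG and IgA only as yes/no against carriage, although the Background suggests that antibody level is what may matter

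*Combined protocol and SAP*

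**What the plan says.** Section 6.22 covers "Pneumococcal IgG and IgA in serum and saliva" and consists of one sentence: "This will be determined yes/no antibody assay result, and compared to the carriage results". Section 6.4 adds only that the main analyses will be descriptive and comparative. Laboratory procedures are left to SOPs (section 4.2.1, Scheduled follow-up).

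On the sample, section 1.4 says "5ml blood and saliva specimens will be obtained from 200 subjects", with collection "before vaccination and then at the 3, 12 and 24 month time-points". The age split is "50 come from children in the age range 30 months to 5 years, 50 from children 6 to 15 years", plus 100 people older than 15 years.

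The Schema describes the survey sample of 1,250 "with a subsample of 200 for 5ml blood specimen and saliva". Section 4.2.1 (Scheduled follow-up) says of the surveys that "separate randomisation procedures will be undertaken for each survey".

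The Background in section 1.1 treats antibody as a matter of degree. It suggests that a weaker replacement effect in one Gambian study may reflect lower concentrations than in a previous one, and that high levels may keep vaccine-type pneumococci from colonising.

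**The concern.** The hypotheses in section 1.1 are about how much antibody a person has, whereas section 6.22 keeps only whether antibody is present. A two-category result cannot show whether carriage falls steadily as concentration rises. It also cannot show a rise between the four collection times in anyone already classed as positive before vaccination.

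There is a cost in precision too. Only 200 subjects give blood and saliva, and dichotomising a graded measurement discards part of what they contribute. How much depends on where the cut falls, which the protocol does not say. If only the category is recorded, the concentration cannot be recovered later.

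**Working it through.** **The plan's own figures.** The protocol states no power, precision or sample-size argument for the antibody comparison, so there is no figure on this point to reproduce. Two side checks:

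- The age strata add up: 50 + 50 + 100 = 200.
- The only stated power, over 90% in section 6.3, concerns carriage. It uses a coefficient of variation of 0.3, 50 subjects per village and 10 or 11 villages per arm. For 30% to 15%, the unmatched cluster formula has variance term 0.30×0.70/50 + 0.15×0.85/50 + 0.3²×(0.30² + 0.15²) = 0.016875. With 10 villages per arm, z = √(9 × 0.15²/0.016875) − 1.96 = 1.50, a power of 93.4%; with 11 it is 95.5%. The stated figure reproduces, and this point does not affect it.

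**Information kept by a yes/no split.** Assume that log antibody is normal and that its relation to carriage is linear. Let p be the share classed positive, z_p the matching normal quantile and φ the normal density. The efficiency of the split relative to the continuous value is

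E = φ(z_p)² / [p(1 − p)]

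The loss is 1 − E, and 200 subjects carry the information of 200 × E. The formula gives the same result for p and 1 − p.

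| Split | φ(z_p) | E | Loss | 200 act like |
|---|---|---|---|---|
| 50/50 | 0.399 | 0.159/0.25 = 0.637 | 36% | 127 |
| 80/20 | 0.280 | 0.0784/0.16 = 0.490 | 51% | 98 |
| 90/10 | 0.175 | 0.0308/0.09 = 0.342 | 66% | 68 |
| 95/5 | 0.103 | 0.0106/0.0475 = 0.224 | 78% | 45 |

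Under these assumptions 36% is the smallest possible loss. It reaches two thirds when about 9.6% fall on one side of the cut, and goes beyond that for more extreme splits.

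**Illustration in power.** Section 6.3 gives vaccine-type carriage as "30% in those aged 30 months or more", which is the age range of the 200. The simulation took 200 subjects, 30% carriage, a two-sided 5% score test, 4,000 runs and an assumed odds ratio of 0.625 per standard deviation of log antibody. Power was 83% for the continuous value. For yes/no it was 66% with half positive, 58% with 80% positive and 48% with 90% positive. The odds ratio is not in the protocol. With 0.7 instead, the continuous analysis had 60% and the 50/50 split 43%.

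These calculations ignore village clustering and repeated measurement. They describe one cross-section of 200 independent people.

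**The case against.** The strongest reply is that the size of the loss is not a property of this plan. It needs a normal log level, a linear effect and a known share positive, and the protocol gives none of these. If antibody protects through a threshold and the cut-off sits there, dichotomising loses little. This stands, and is why the figures are conditional. It does not rescue section 6.22, which names no threshold. Analysing concentration still allows a prespecified cut-off to be tested; keeping only yes/no does not allow the reverse.

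A second reply is that an SOP may record numeric values. That is possible, but section 4.2.1 refers laboratory procedures to SOPs, and the analysis stated in section 6.22 is still binary.

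A third is that antibody appears in none of the objectives in section 2.0, so this comparison is supportive. That is right, and it limits the weight of the point.

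A reader might go further than the documents allow in four ways:

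- **That this is the trial's only mechanistic analysis.** Section 6.21(c) also lists the rate of capsular switching, which section 1.1 discusses as part of the replacement mechanism.
- **That yes/no hides all change after vaccination.** If the same people are followed, conversion from negative to positive is visible. Only graded change is lost.
- **That the comparison is confounded by age.** Section 6.22 neither requires nor excludes an age-specific comparison, and the age strata make one possible. The fair statement is that no adjustment is specified.
- **That few of the 200 would have a paired swab.** Chance overlap of a fixed 200 with a redrawn survey would give about 200 × 1,250/6,000 = 42. But the Schema nests the 200 within the 1,250, and section 1.4 says that each survey subject is swabbed immediately before it describes the blood and saliva sample. Nesting is the more natural reading. What remains is an ambiguity about whether the 200 are fixed or redrawn.

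**Conclusion.** The point holds as a weakness in the planned analysis. Section 6.22 commits to a binary antibody result with no cut-off, while section 1.1 frames the question, in cautious terms, as one of level. Dose-response, and graded change in those already positive, cannot be examined as planned.

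The loss of information runs from 36% at an even split to 78% at 95/5, given approximate normality of log antibody and a linear relation to carriage. It would be unsafe to quote a single range as a fact about this trial: the share positive is unknown, extreme splits lose more, and a true threshold at the cut-off could make the loss small. That most samples would be positive is a possibility, not something the protocol documents.

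The carriage outcomes and their stated power are unaffected. The change is nevertheless worth making before assay results are reported, because it depends on numeric values being retained.

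**What to change.** Rewrite section 6.22 to say:

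- The numeric assay readout is retained, and log antibody concentration is the main analysis, summarised as geometric means by arm, age group and time-point for each of IgG and IgA in serum and saliva.
- Same-visit carriage is modelled on log concentration, matching each serotype's antibody to carriage of that serotype, or using one prespecified vaccine-type summary. The model adjusts for age group and arm, with random effects for village and person.
- A yes/no result at a cut-off defined in advance is secondary.

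Separately, reconcile the Schema, section 1.4 and section 4.2.1 (Scheduled follow-up) on whether the 200 are one fixed cohort or are redrawn within each survey sample. The person random effect and any within-person change depend on the answer. Also state which swab is paired with the pre-vaccination sample, since section 4.2.1 (Screening at the villages) lists blood and saliva at that visit but no swab.

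The cost is keeping the numeric values and a little more analysis work. Serotype-specific results should be labelled exploratory: at 30% vaccine-type carriage there would be about 0.30 × 200 = 60 carriers, or 60/7 ≈ 9 per serotype if evenly spread across the seven (an assumption), and fewer if vaccination lowers carriage.
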